### Study design

Potentially eligible patients who are scheduled for cardiac surgery will be contacted via telephone, during preoperative hospital admission or during a preoperative hospital visit. Patients will receive both written and oral information (online supplemental file 1). After informed consent is obtained and signed, baseline characteristics such as age, sex, ethnicity, BMI, blood pressure, American Society of Anesthesiologist physical status, medical history and medication use will be collected. The most recent serum creatinine and glycated haemoglobin A1c, if measured as part of standard medical care before surgery, will be recorded. Patients will subsequently be randomised to dapagliflozin or placebo. Patients will take the first dapagliflozin 10 mg or placebo on the day before surgery, between 15.00 and 20.00. The second dosage will be taken on the morning before surgery. The remainder dosages will be taken the first and second day after surgery. In case the surgery is postponed, an additional dose will be administered. Patients with T2D on glucose lowering therapy will be advised on how to adjust their current diabetes treatment to prevent potential hypoglycaemia (figure 2).

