### Outcomes and outcome adjudication

The primary outcome of this study is the incidence of AKI according to the KDIGO criteria (table 2) based on serum creatinine and urine output. Serum creatinine levels and urine output will be reviewed by a second investigator and the study monitor to ensure primary outcome adjudication. Other secondary kidney-related outcome parameters include the difference in the primary outcome between men and women, incidence of individual AKI stages according to KDIGO criteria, the maximum change of creatinine postoperatively compared with the baseline creatinine preoperatively, the postoperative creatinine course, the number of patients with persistent kidney failure (defined as creatinine concentration ≥200% of baseline creatinine concentration after 30 days), the number of patients requiring dialysis and the number of patients who died due to a primary kidney-related cause. The cardiac-related secondary outcomes include the incidence of de novo postoperative atrial fibrillation, registered on a 12-lead ECG, the maximum postoperative creatine kinasemyocardial band (CK-MB) or troponin concentrations, the number of patients who developed new onset cardiac arrhythmia, new myocardial infarctions or cerebrovascular accident confirmed by CT scan within the first 30 days postoperatively, as well as the number of patients who required an extended hospital stay due to heart failure, needed readmission for heart failure or died from a primary cardiac cause. Furthermore, length of stay in the ICU and the hospital measured in days and all-cause mortality were collected (table 3). Complications within the first 30 days after surgery (online supplemental table 1) are retrieved from the electronic patient file and collected. The outcomes of the patient-reported quality of life and disability measured with three questionnaires, DAH30,^19^ WHO-DAS 2.0^20^ and EQ5D5L,^21^ will be evaluated across the treatment groups. Safety outcomes of SGLT2 inhibitors such as genital mycotic infections, DKA and hypoglycaemia will be assembled and compared between the treatment groups.

**Table 2 T2:** Definition and staging of acute kidney injury according to kidney disease: improving global outcomes criteria

Stage	Acute kidney injury	Difference	Time frame
1	Serum creatinine	≥0.3 mg/dL (26.5 mcmol/l) or	Within 48 hours
		≥1.5 times baseline	Within 7 days
	Urine output	<0.5 mL/kg/h	For 6–12 hours
2	Serum creatinine	2.0–2.9 times baseline	

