	Urine output	<0.5 mL/kg/h	For >12 hours
3	Start renal replacement therapy		
	Serum creatinine	3.0 times baseline or	Within 7 days
		≥4.0 mg/dL	
	Urine output	<0.3 mL/kg/h or	>24 hours
		Anuria	>12 hours

**Table 3 T3:** Recorded secondary and exploratory outcomes

Outcome measures	Time frame	Definition
Secondary outcomes		
Individual AKI stages	≤ 7 days postoperative	Incidence of stage 1, 2 and 3 AKI according to KDIGO criteria
Creatinine	≤ 7 days postoperative	Postoperative maximum change of creatinine compared with baseline creatinine
AF	≤ 7 days postoperative	Postoperative AF recorded with an ECG or for which treatment is initiated
LoS-ICU	≤ 30 days postoperative	LoS-ICU, measured in days from transfer to ICU until discharge from ICU
LoS-Hos	≤ 30 days postoperative	LoS-Hos, measured in days from surgery until discharge from the hospital
MAKE	≤ 30 days postoperative	MAKE. Composite endpoint of death, new dialysis and worsened renal function
MACE	≤ 30 days postoperative	MACE. Composite endpoint of cardiovascular death, nonfatal myocardial infarction, nonfatal ischaemic cerebral vascular accident and hospitalisation for heart failure
Safety outcomes	≤ 30 days postoperative	Genital mycotic infections, diabetic ketoacidosis and hypoglycaemia
Hypoglycaemia	≤ 3 days postoperative	Incidence of hypoglycaemia (blood glucose <4 mmol/L) detected during routine perioperative glucose measurements
Hyperglycaemia	≤ 3 days postoperative	Incidence of hyperglycaemia (blood glucose >10 mmol/L) detected during routine perioperative glucose measurements
Cardiac biomarker 1: troponin	From transfer to ICU until 48 hours postoperatively	Peak troponin concentration as routinely measured during clinical practice
Cardiac biomarker 2: CK-MB	From transfer to ICU until 48 hours postoperatively	Peak CK-MB concentration as routinely measured during clinical practice
Patient-reported quality of recovery 1	Recorded at 30 days postoperatively	According to Days at Home in first 30 days
Patient-reported quality of recovery 2	Recorded at 30 days postoperatively	According to WHO Disability Assessment Schedule 2.0
Patient-reported quality of recovery 3	Recorded at 30 days postoperatively	According to 5 level EuroQol 5-Dimensions questionnaire
Exploratory outcomes		
Systemic haemodynamics 1	From start of anaesthesia until discharge from the ICU, assessed up to 72 hours	Perioperative hourly average heart rate

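### Table 3 times its safety outcomes from surgery although two of the four planned doses come before it, and lists hypoglycaemia in two unreconciled rows

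*Protocol article*

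**What the plan says.** All references are to the Protocol article.

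**Dosing (Study design).** "Patients will take the first dapagliflozin 10 mg or placebo on the day before surgery, between 15.00 and 20.00". Another dose follows in the morning, still ahead of the operation, and the last two are planned for postoperative days 1 and 2. For delays: "In case the surgery is postponed, an additional dose will be administered". The same section says that patients with type 2 diabetes on glucose-lowering drugs will be "advised on how to adjust their current diabetes treatment to prevent potential hypoglycaemia".

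**Safety outcomes (Outcomes and outcome adjudication, with Table 3).** The text promises a between-group comparison of the known risks of the drug class and gives no window for it. Table 3 has a safety row, "Genital mycotic infections, diabetic ketoacidosis and hypoglycaemia", timed up to 30 days postoperative. A separate hypoglycaemia row is timed up to 3 days postoperative and defined as "Incidence of hypoglycaemia (blood glucose <4 mmol/L) detected during routine perioperative glucose measurements". For complications, the text counts "Complications within the first 30 days after surgery".

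**Drop-outs (Achieve sample size).** Cancellation of surgery is given as an example of drop-out, and drop-outs are to be replaced.

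**The concern.** A safety comparison should cover the time during which patients are exposed, in all patients who were exposed. Here exposure starts the day before surgery, while the stated windows are measured from surgery.

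The interval left out is not free of the risks the trial wants to compare. The article adjusts diabetes treatment because of hypoglycaemia, and Trial population excludes several groups because of ketoacidosis. Both are named safety outcomes. A patient who takes study drug and is then cancelled has no postoperative day at all. If the event itself led to the cancellation, the comparison as worded would not contain it.

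Hypoglycaemia has a further difficulty. It appears twice with different time frames, and the article does not say whether these are one outcome or two, or which of them the promised comparison uses.

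**Working it through.** The plan states no safety event rate, so there is no safety figure to reproduce. The check is a count of doses and a side-by-side reading of the windows.

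**1. Doses relative to surgery (Study design).**
- Planned: day before, morning before surgery, day 1 after, day 2 after = 4.
- Before surgery: 2. Share = 2/4 = 50%.
- With one postponement, assuming that the single extra dose falls before surgery: (2 + 1)/(4 + 1) = 3/5 = 60%.

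**2. Length of the interval.** The article gives no operating time. Assume a start at 08.00, purely for illustration.
- First dose at 20.00: 12 h before surgery. First dose at 15.00: 17 h before surgery. Later operations lengthen both.
- Share of a window from first dose to day 30 (30 × 24 = 720 h after surgery): 12/(720 + 12) = 1.6% to 17/(720 + 17) = 2.3%.
- Share of a window from first dose to day 3 (72 h after surgery): 12/(72 + 12) = 14% to 17/(72 + 17) = 19%.

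Half the doses is therefore not half the time at risk. The gap is small against 30 days and appreciable against 3 days.

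**3. Where the windows open.**
- Both safety rows in Table 3 are in postoperative days, a unit that starts at surgery.
- Complications in the outcomes text are also counted from surgery.
- Study design says only how long complications are registered and names no start.
- Where Table 3 wants another start it names one: the haemodynamic rows begin with anaesthesia and the cardiac biomarkers with arrival in the ICU. No row names the first dose.

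**4. The two hypoglycaemia entries.**

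| | Separate row | Within the safety row |
|---|---|---|
| End of window | day 3 | day 30 |
| Threshold | <4 mmol/L | none |
| Source | routine perioperative glucose | none |

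The windows differ by 30 − 3 = 27 days. A low glucose on day 10 could be a case under the second entry but not under the first. The first entry also conflicts with itself: perioperative measurements can include pre-operative ones, while its time frame is postoperative.

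**5. Effect on the contrast.** Let q be the proportion of an arm whose only event falls before surgery. Then

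RD(from first dose) = RD(from surgery) + (q for dapagliflozin − q for placebo).

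Leaving out the interval cannot raise either arm's count. The difference between arms can move in either direction, and neither q is given or can be derived.

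**The case against.** The strongest reply is that the article never says pre-operative events are excluded. The upper limits in Table 3 fix an end, Study design gives only an end for complication registration, and the three-day row speaks of perioperative glucose. That leaves some room on the start. It does not settle the matter, because no passage includes the pre-operative interval and Table 3 does name a different start where it wants one.

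A second reply is that Study oversight and organisation covers serious events without limiting them to the time after surgery. This stands: a serious ketoacidosis before surgery would still be reported, and a reader should not infer that serious-event reporting begins at surgery. But that reporting is not the between-group comparison, and a glucose below 4 mmol/L need not be serious.

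A third reply is that this is a condensed article, and that safety populations and collection dates often sit in the full protocol or the SAP. Their absence would be no finding. The point rests on what the article does print: windows tied to surgery, and two entries for one outcome in one table.

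Four stronger readings are tempting and not supported:
- *The hypoglycaemia rate is undefined.* The three-day row has a threshold, a source and an end, and the two rows may well be two intended outcomes.
- *The comparison can only understate harm.* Step 5 shows that this holds for the counts in each arm, not for the contrast.
- *Up to four of six doses could precede surgery.* This is inferred from the six capsules per box. The article speaks of a single additional dose and does not say what the spare capsules are for.
- *The pre-operative data are already on file.* The article does not say where the first dose is taken or whether glucose is measured that night.

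**Conclusion.** The point holds as a defect in the wording of the secondary safety outcomes. Read literally, the planned comparison omits the interval from first dose to surgery, during which two of the four planned doses (50%) are taken, and has no window for patients who are dosed and then cancelled. Hypoglycaemia stands in two unreconciled entries. One is defined but conflicts internally on timing, and the other has no threshold or source.

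The 60% figure assumes that one extra dose falls before surgery, and the 12 to 17 hours assume an 08.00 operation. Without event rates, neither the number of events affected nor the direction of any shift between arms can be stated. The primary AKI analysis and the sample size of 784 do not depend on this. The change is worth making before database lock because it alters what is counted.

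**What to change.** 1. Open the Table 3 safety windows and the complication window at the first dose of study drug. Keep the stated end at 30 days after surgery. If surgery does not take place, end at a fixed time after the last dose.
2. Compare safety in all patients who took at least one capsule, including those whose surgery was cancelled and who were replaced for the efficacy target.
3. State that the two hypoglycaemia rows are separate outcomes: glucose below 4 mmol/L on routine measurements from first dose to postoperative day 3, and clinically reported events to day 30. Give the second its own definition, and say which one is the main safety comparison.

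The cost is revised outcome wording and a changed start date in data capture, with some extra event recording and short follow-up of cancelled patients. Pre-operative glucose will be limited to what is routinely measured, and the report should say so. Neither dosing nor clinical care changes.

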## Methods

The MERCURI-2 trial (clinicaltrials.gov identifier: NCT05590143) is a multicentre randomised triple-blind placebo-controlled (1:1) superiority trial in patients undergoing cardiac surgery. The trial is designed to evaluate the effect of dapagliflozin 10 mg once daily, compared with placebo, added to standard of care, on the incidence of CSA-AKI. This is an investigator-initiated study, with Amsterdam UMC as sponsor. The study protocol was approved by the Medical Ethics Committee of the Amsterdam UMC and by the Competent Authorities according to national and international regulations (METC 2022.0795 and EudraCT number 2022-002453-25). The first patient was included in June 2023. The trial has an estimated duration of 3 years.

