### Randomisation

After inclusion, patients will be randomised by Castor EDC. Block randomisation with computer-generated blocks of 4, 6 or 8 patients will be used. The block size will be unknown to the researchers. Randomisation is stratified for sex, presence of T2D and study site.

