### Sample size calculation

Sample size is based on Fisher’s exact test, with an expected AKI incidence in the placebo group of 22%, based on previous cohorts,^2^ taking a conservative estimation. A relative risk of 0.64 based on AKI reduction by SGLT2 inhibitors in previous trials^6^ translates into an absolute risk reduction of 7.9% and incidence in the intervention group of 14.1%. The required total sample size to find such a difference with two-sided alpha of 0.05 and 80% power is 784. We therefore aim to include 392 patients per arm.

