### Secondary study outcomes

Heterogeneity of treatment effect between men and women will be studied for the primary outcome by examining a treatment-by-sex interaction effect in a logistic regression model with treatment and sex as main effects. Similarly, the heterogeneity of treatment effect in patients with and without T2D will be studied using the same approach. Treatment effect estimates, along with their corresponding 95% CIs, will be reported for each specific subgroup. Other secondary outcomes will be presented as number of events and analysed with the Fisher’s exact test. Continuous data will be presented as mean with SD and differences will be assessed employing the Student’s t-test. Generalised mixed-effect models will be constructed to examine potential differences in the repeated measurements. Predefined post hoc analysis with regression analyses will be conducted to estimate the influence of age, BMI, baseline kidney function and the presence of heart failure on the treatment effect and their possible interactions on the primary outcome. A 2-sided p value <0.05 will be considered statistically significant. Statistical uncertainty will be expressed in 2-sided 95% CIs.

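### Peak troponin and CK-MB are local routine values in a multicentre trial, but the stated t-test on means has no site or assay term; if assays differ between sites, precision and interpretability suffer

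*Protocol article*

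**What the plan says.** Under Methods, the protocol article describes a "multicentre randomised triple-blind placebo-controlled (1:1) superiority trial". Under Randomisation it states: "Randomisation is stratified for sex, presence of T2D and study site".

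Table 3 lists two cardiac biomarkers among the secondary outcomes, both from ICU transfer to 48 hours after surgery. One is "Peak troponin concentration as routinely measured during clinical practice"; the other is "Peak CK-MB concentration as routinely measured during clinical practice". The text of Outcomes and outcome adjudication words this differently, as "the maximum postoperative creatine kinasemyocardial band (CK-MB) or troponin concentrations".

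For the analysis, the section Secondary study outcomes says: "Continuous data will be presented as mean with SD and differences will be assessed employing the Student’s t-test". It adds no site term, transformation or scaling. Mixed-effect models are reserved for repeated measurements, and a peak is one value per patient.

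**The concern.** The article fixes two things that may not fit together. The values come from each hospital's own routine measurement, and the comparison is an unadjusted t-test on their means. If two hospitals report troponin on different scales (troponin T against troponin I, different assays, different units), three things follow:

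- The arm mean is a mixture without a clear unit, set mostly by the sites with the larger numbers.
- The spread between assays enters the error term, so a real difference in myocardial injury is harder to detect.
- A null result is harder to read, because it could reflect mixed scales as well as the absence of an effect.

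This is a different problem from skewness. A log transform or a rank test deals with skewness but leaves the difference between assays in the error.

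**Working it through.** **The plan's own figure.** The article gives no power figure for the biomarkers. Its only sample size is 784 (392 per arm) for AKI, 22% against 14.1%. Exact enumeration of Fisher's test at 392 per arm gives power 0.800, so that figure reproduces and is not in question. It supplies n = 392 below.

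**Assumptions, none from the documents.** Peaks are lognormal with log-SD s = 0.8 or 1.0. The true geometric mean ratio is 0.80. Two assays differ by a constant factor k, with half the patients on each and balance between arms. Every patient has a value.

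**Log scale with an assay term.** The standard error is SE = s√(2/n).
- s = 0.8: 0.8 × √(2/392) = 0.0571. |ln 0.80| = 0.2231, so power = Φ(0.2231/0.0571 − 1.96) = Φ(1.95) ≈ 97%.
- s = 1.0: SE = 0.0714, so power = Φ(3.12 − 1.96) = Φ(1.16) ≈ 88%.

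The factor k drops out, so these hold at every ratio, including k = 1.

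**Log scale without an assay term.** At equal split the assay adds (ln k)²/4 to the variance that the test uses. Because assay is balanced between arms, the true sampling error of the difference stays at s√(2/n). Power = Φ((0.2231 − 1.96 × SE_used)/(s√(2/n))). At k = 10, (ln 10)²/4 = 1.326.
- s = 0.8: SE_used = √(2/392 × (0.640 + 1.326)) = 0.1001, so power = Φ((0.2231 − 0.1962)/0.0571) = Φ(0.47) ≈ 68%.
- s = 1.0: SE_used = √(2/392 × 2.326) = 0.1089, so power = Φ((0.2231 − 0.2135)/0.0714) ≈ 55%.

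**Simulated power** (thousands of trials per setting; repeat runs agree within a few points, and the log columns match the formulas above). Entries are for s = 0.8 / 1.0.

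| Scale ratio k | Raw t-test | Log, no site term | Log with site/assay term |
|---|---|---|---|
| 1 (one assay) | 91% / 68% | 98% / 88% | 97% / 88% |
| 2 | 86% / 63% | 96% / 85% | 97% / 88% |
| 3 | 78% / 53% | 94% / 80% | 97% / 88% |
| 10 | 57% / 39% | 67% / 56% | 97% / 88% |

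A rank test on pooled values at 10-fold gives 62% / 49%.

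**Separating skewness from assay mixing.** The first row shows what skewness alone costs the raw t-test: 98 − 91 = 7 points and 88 − 68 = 20 points. Only the fall down the raw column is due to mixing: 91 − 86 = 5 and 68 − 63 = 5 points at 2-fold, 13 and 15 at 3-fold, 34 and 29 at 10-fold.

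**Efficiency of the raw t-test relative to the same test on one scale.** Let A = mean(c²)/(mean c)², where c is the assay factor. Relative efficiency = (e^{s²} − 1)/(A·e^{s²} − 1). This was computed at s = 1.0 and s = 0.7.
- 2-fold: A = 2.5/2.25 = 1.111. Efficiency is 1.718/2.020 = 0.851 and 0.777, a loss of 15% to 22%.
- 5-fold: A = 13/9 = 1.444. The loss is 41% to 53%.
- 10-fold: A = 50.5/30.25 = 1.669. Efficiency is 1.718/3.538 = 0.486 and 0.367, a loss of 51% to 63%.

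At 10-fold, the assay with the larger numbers supplies 10/11 = 91% of the pooled mean.

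**Type I error.** With no treatment effect and s = 1.0, the raw pooled t-test rejects in 0.044 of trials with one assay, 0.027 at 10-fold and 0.023 at 100-fold. It becomes conservative, as the overstated standard error implies.

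**The case against.** The strongest reply is that the central premise is not in the document. Nothing says that any two sites use different troponin or CK-MB assays, how many sites take part, or how patients are divided between them. Local measurement at several centres makes mixed assays possible and no more. This stands, and the point is conditional for that reason. It also rules out a reading that a reader might be tempted by, that values on different scales are in fact being averaged and that a null result would be due to it.

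A second reply is that assay names, units and reference limits belong in the full protocol, the data management plan or an analysis plan, none of which is shown. This also stands: their absence from an article is not the finding. What remains is what the article does state, namely the source of the values and the test. A harmonisation step elsewhere would help, but the stated test would still lack the stratification factor.

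Third, the Statistical analyses section lets description depend on distribution (mean or median), so the t-test might not be used on skewed peaks. That would address skewness, not scale: at 10-fold, neither the log transform nor the rank test on pooled values restores the power.

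Fourth, the loss is modest if scales are close. At 2-fold, a log analysis without a site term loses only 1 to 3 points against the adjusted one. This is correct.

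Finally, Table 3 already keeps the two markers apart, so the word joining them with an alternative in the text is a wording mismatch. This is accepted.

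**Conclusion.** The point holds in conditional form. For two secondary outcomes built on local routine values, an unadjusted t-test on raw means is a poor choice when site is already a stratum and a model with site/assay costs nothing if all sites share one assay (about 97% / 88% power either way).

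The size depends on an unknown scale ratio. In the assumed scenario, mixing costs the raw t-test about 5 points of power at 2-fold, 13 to 15 at 3-fold and 29 to 34 at 10-fold, on top of what skewness already costs. A reader might infer that most of the information is lost; that needs roughly a 5- to 10-fold difference and is not shown. A reader might also infer bias. Stratification by site balances the assay mix between arms in expectation, and type I error falls instead of rising. The primary AKI outcome and the 784 are untouched.

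The figures rest on lognormal peaks, the chosen log-SDs, an equal split, a constant multiplicative difference between assays, and a value for every patient. The last is optimistic for a marker taken from routine care.

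**What to change.** For these two outcomes, replace the t-test on raw means with a linear model on log peak, or on the log of the multiple of the assay's upper reference limit. Include treatment and site/assay as terms, and report a ratio of geometric means with its 95% CI. Analyse troponin and CK-MB separately.

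Record the assay, troponin type and unit for each site, and the upper reference limit if that scaling is used.

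Reword the sentence in Outcomes and outcome adjudication so that it names the same two outcomes as Table 3.

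The cost is one data entry per site and one changed model line, with no new samples. Investigators stay blinded until database lock, so the change can be made without knowledge of results. The downside is that readers receive a ratio instead of a difference in concentration.
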